## Methods/design

### Design

The ELMS is a randomised control trial, that investigates whether an intervention based on BA principles improves life engagement and wellbeing compared to an active control condition, specifically a multi-component positive psychology intervention (MCPPI). Participants will be randomly allocated to one of the two conditions (BA, MCPPI) and will take part in an intervention consisting of six weekly one-on-one sessions of up to one hour, to be administered by trained facilitators via telephone or web conferencing (based on participants’ preference). Program efficacy will be determined by assessment at three time points: baseline (pre-intervention), 1 week and 3 months post intervention. All participants will also complete a daily questionnaire for two weeks between sessions 4 and 6. A summary of the study periods and assessments are provided in Table 1.

**Table 1 Tab1:** Summary of study phases and assessment measures

Time point	Pre-program	Baseline	Program (6 weeks)	1-week post-program	3-month post-program
Enrolment					
Eligibility screen (Life Engagement Test)^a^	X				
Informed consent	X				
Allocation to condition	X				
Intervention					
Treatment: BA			↔		
Active control: MCPPI			↔		
MOCA-blind			X (wk 5)		
Daily questionnaire (2 weeks)			X (wk 4–6)		
Assessment					
Demographics		X			
Alcohol and tobacco use		X			
Pain and physical health		X		X	X
SPANE		X		X	X
Self-compassion scale		X		X	X
BADS		X		X	X
HADS		X		X	X
Life engagement test		X		X	X
UCLA loneliness scale		X		X	X
Flourishing scale		X		X	X
Satisfaction with life scale		X		X	X
Engaged living scale		X		X	X
Social networks scale		X		X	X
Goal adjustment scale		X		X	X
Client satisfaction questionnaire				X	
Daily questionnaire assessment					
State self-compassion			X		
Daily affect scale			X		
DISE			X		
Eudaimonic wellbeing			X		

*BA* Behavioural activation;* BADS*  Behavioural Activation for Depression Sale;* DISE*  Daily Inventory of Stressful Events;* HADS* Hospital Anxiety and Depression Scale;* LET* Life Engagement Test;* MCPPI* Multi component positive psychology intervention;* SPANE* Scale of Positive and Negative Experience

^a^Participants are eligible if they score at or below the mean LET reported in previous studies (see *Participants*)

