### Study timeline

Older adults who are on a pre-existing list maintained by the Adult Development Lab will be initially contacted by telephone by a research assistant. They will be provided with details of the study, and if they indicate they are interested in participating, they will be administered the LET over the phone to assess their eligibility to participate. Participants who are recruited by online advertisements will be invited to follow a link where they will be provided some information about the study and invited to complete the LET online to determine eligibility. Participants undertaking the full 6-item LET at telephone screening will be eligible to participate if they score at or below 25. Participants undertaking the online screening will be administered a 5-item version of the LET and will be eligible if they score at or below 21 (the mean of the 5-item scale in a community sample of older adults assessed as part of the broader project, N = 431). The final LET item “I have lots of reasons for living” will be excluded for online participants to reduce the possibility of negative feelings among some participants, given that the item would not appear within the context of either a larger survey, or with the presence of the telephone interviewer as an immediate source of support and/or information. The decision to exclude the final item from the online screener was also based on previous data indicating strong item-specific ceiling effects (M = 4.43 (SD = 0.86) on a scale of 1 to 5; [32]) suggesting limited discriminatory value. All eligible participants will be sent, by post or email, the study information sheet, consent form and baseline questionnaire (marked with a unique 3-digit identifier) to complete and return. Those who elect to receive the baseline by email will be sent a link to the baseline questionnaire hosted on the Qualtrics Online Survey Platform. Once the baseline questionnaire is completed participants are considered fully recruited into the study. Using simple randomisation via Microsoft Excel, participants are then allocated to treatment condition. Randomly allocated to treatment condition, sent the corresponding intervention manual and allocated to a study facilitator. The facilitator will contact the participant by telephone to set up a time for the first session and will be responsible for all contact from that participant from then on.

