Participants will then undergo six weekly sessions conducted either via the telephone or via online video conferencing software. A graphical representation of the study timeline is provided in Fig. 1. Between each session they will be provided with some activities to complete. For those in the BA group, the between session activities will be flagged as particularly important to complete. If they are not completed during the week, they will be completed with the facilitator during the next session, as per BA protocol [22]. The MCPPI group will be encouraged to complete the between session activities. Facilitators will track their progress on running sheets which will be used to guide content delivery, document participant adherence and make note of anything relevant that may impact delivery or progress. For two weeks during the fourth and fifth weeks of the intervention, participants will be asked to complete a daily questionnaire, which will be posted to them with a reply-paid envelope to return once completed. It is anticipated these questionnaires will take less than 5 min per day to complete. At the end of the fifth session, participants will undergo the MOCA-Blind [57]. Once they have completed the intervention, participants will be posted or emailed two follow-up questionnaires; the first at one week post intervention, and second at three months post intervention. It is anticipated these will take approximately 30 min each to complete. Once their first follow-up assessment is returned, participants will be sent $100 (AUD) reimbursement for their time in the form of a pre-loaded EFTPOS card.

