### Sample size and analysis

Sample size considerations were based on the numbers of participants needed to detect a medium effect size difference between the BA and active control groups on the LET at 1-week post intervention. This represents a difference of approximately 2-units on the LET based on previous research (possible scores range from 6 to 30) [32]. Positive psychology interventions have typically been found to have effect sizes in the small to medium range; for example, a recent meta-analysis reported values ranging from *g* = 0.39 to *g* = 0.62 across mental health and well-being outcomes [39]. Within this range, we deemed a medium effect as being a reasonable marker of meaningful change in life engagement, given that our exclusion criterion (see *Participants*) excluded those already scoring at or near the maximum on the LET. Using the Stata “power” module with alpha = 0.05 and a group difference of *d* = 0.52 indicated that 60 participants per group are required for power = 0.8. Data will be analysed using linear mixed models, which allow for dependencies among repeated observations, as is the case with pre- and post-test data (e.g., [63]). Models will be specified taking into account guidelines provided by Twisk et al. [64] for estimating treatment effects in randomised controlled trials. Specifically, a mixed model will be specified that includes dummy variables for time (contrasting baseline with 1-week and 3-month follow-ups) and interactions of time with treatment (BA vs. MCPPI) to estimate treatment effects at the first (1-week) and second (3-month) follow-ups. This approach controls for treatment group differences at baseline and makes use of all available data, with missing data accommodated under FIML assumptions [65].

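### Both follow-up questionnaires are tied to completing the intervention, and the protocol states no follow-up for randomised participants who stop early

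*Protocol article*

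**What the plan says.** In Study timeline, the questionnaires that carry the primary outcome are sent after the programme: "Once they have completed the intervention, participants will be posted or emailed two follow-up questionnaires". The same sentence counts their dates from the programme's end, at one week and at three months. Both dispatch and dating therefore hang on the end of the intervention.

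The Design section states the schedule without a completion condition: "Program efficacy will be determined by assessment at three time points: baseline (pre-intervention), 1 week and 3 months post intervention". The Abstract and the Assessment section likewise count follow-up from the end of the programme. None of these places says what happens to a participant who stops partway.

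Randomisation comes after baseline: "Once the baseline questionnaire is completed participants are considered fully recruited into the study", and allocation follows. Every randomised participant should therefore have a baseline LET. Table 1 shows the LET at baseline and the two follow-ups, with none during the six weeks.

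The analysis in Sample size and analysis is a linear mixed model with "interactions of time with treatment (BA vs. MCPPI) to estimate treatment effects at the first (1-week) and second (3-month) follow-ups". It "makes use of all available data, with missing data accommodated under FIML assumptions". No completer or per-protocol set is defined.

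**The concern.** Completing the programme happens after randomisation and may depend on the arm and on how well the programme is working. If that event decides who is asked for the primary outcome, the groups compared at follow-up are no longer the groups that were randomised.

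A person who stops at session 3 never meets the stated trigger, and the follow-up date has no defined starting point for them. Such people would be missing at both follow-ups by design of the mailing, not because they declined to answer. No later analysis plan can recover a questionnaire that was never sent.

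Stopping could differ between arms. In Study timeline, "For those in the BA group, the between session activities will be flagged as particularly important to complete", and missed BA tasks are made up at the next session, whereas control participants are only encouraged to do theirs. This is a reason to guard against unequal stopping, not evidence that it will occur.

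**Working it through.** **1. The plan's own sample size.** Inputs from Sample size and analysis: d = 0.52, alpha 0.05 (two-sided assumed), power 0.8, for the "difference between the BA and active control groups on the LET at 1-week post intervention". The normal approximation gives 59 per group. The exact two-sample t test gives power 0.7998 at 59 and 0.806 at 60, so the stated 60 per group reproduces. Two LET units at d = 0.52 imply an SD of 2 / 0.52 = 3.85. The Abstract's target of 120 or more equals 2 x 60, with no stated margin for loss.

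**2. What an early stopper contributes.** Under the literal reading: baseline LET observed, 1-week and 3-month LET missing. The model keeps this person, but their follow-up is in effect predicted from baseline using the relation seen in those with follow-up. That is sound only if, given baseline LET, stoppers would have scored like completers in their arm.

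**3. Illustration A: stoppers gain nothing.** Assumptions, not in the article: a proportion p of the BA arm stops, completers gain 2 units over control, stoppers gain 0, and stopping is otherwise unrelated to outcome.

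- Effect in all randomised = 2 x (1 - p).
- p = 0.10: 2 x 0.90 = 1.8 units. p = 0.25: 2 x 0.75 = 1.5 units.
- The observed BA follow-ups come only from people with the 2-unit gain, so the model reports about 2.0.
- Ratios: 2.0 / 1.8 = 1.11 and 2.0 / 1.5 = 1.33.

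**4. Illustration B: unequal stopping, an alternative to A.** Assume 20% stop in BA and 10% in control, with stoppers in both arms 2 to 3 units below the model's prediction. Bias = (0.20 - 0.10) x 2 = 0.2 to (0.20 - 0.10) x 3 = 0.3 units. This must not be added to A, which already puts BA stoppers 2 units below prediction. Adding the two would need BA stoppers 4 to 5 units below, more than one SD of 3.85.

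**5. Simulation.** 10,000 trials of 60 per arm, true effect zero, baseline-to-follow-up correlation 0.5, about 24% stopping in BA and 10% in control (random in control), all stoppers without follow-up. A baseline-adjusted estimate stands in for the planned mixed model. All settings are assumptions.

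| BA stopping depends on | Bias, raw completer difference | Bias, baseline-adjusted |
|---|---|---|
| Baseline score | 0.10 SD | 0.00 SD |
| Unseen follow-up score | 0.20 SD | 0.16 SD |

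0.16 SD is about 0.6 LET units (0.16 x 3.85), against a target of about 2.

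**6. Power.** If a share of each arm has no follow-up (assumed), power under the plan's own t-test calculation falls from 0.81 to 0.76 at 10% (54 per arm) and 0.71 at 20% (48 per arm).

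**The case against.** The strongest reply is that the sentence describes timing. The paragraph walks through the expected path (six sessions, a cognitive screen after the fifth, then questionnaires) and assumes that everyone progresses. It does not say that questionnaires go only to completers, and the Design section and Table 1 set no such condition. Procedures for withdrawals, and the naming of the analysis population, are commonly left by an article to the full protocol or analysis plan. This stands in part. Silence on withdrawals would not by itself be a finding, and the timing reading is possible, which lowers the severity. But the one operational rule that is stated uses completion as its trigger, and nothing else in the article corrects it.

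A reader might go further and infer that non-completers have no outcome data and that the trial becomes a completer analysis. The documents do not support that. Baseline LET exists for everyone randomised, and the plan is a likelihood-based model on all available data. Step 5 shows the difference: where stopping depends on baseline, the raw completer difference is biased and the adjusted estimate is not. What remains is reliance on missing at random, with little beyond baseline LET to make it plausible.

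It is also fair that unequal stopping is conjecture. The active control section describes the arms as comparable in time and effort. Planned session time is similar, at 255-285 minutes for BA and 240-260 for control (sums of Tables 2 and 3), and making up BA tasks in session eases the burden. Finally, the reimbursement already depends on returning the first follow-up, not on attendance.

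**Conclusion.** The concern holds as a fault in how follow-up is fixed. The stated trigger and clock for both follow-ups is completion of the intervention, and no follow-up is provided for randomised participants who stop early. Applied literally, the 1-week and 3-month contrasts would rest on completers' follow-up values and be unbiased only if stopping is unrelated to the unseen outcome given baseline LET.

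The size cannot be known from the article, which gives no non-completion rate. The gap of 0.2 to 0.5 units in illustration A (2.0 against 1.8-1.5), the 0.2-0.3 units in B and the 0.6 units in the simulation are separate scenarios under assumed rates and mechanisms. None is an estimate for this trial, and an overstatement of 11-33% should not be read as a finding. If stopping is rare, or depends only on baseline LET, the bias is negligible. Severity is moderate, because the sentence may have been meant as timing only.

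**What to change.** Amend Study timeline to say that every randomised participant is sent both questionnaires, whatever number of sessions was attended, at dates fixed from randomisation or from the scheduled first session and matched to the planned 1-week and 3-month post-programme points. State that the existing reimbursement on return of the first follow-up applies to all. If the sponsor already follows early stoppers, the same sentence records it.

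The cost is a wording amendment, a date-driven mailing list, and a few extra mailings, reminders and reimbursements. Participants whose sessions are postponed will be assessed closer to their last session than planned, so the amendment should say how much slippage is allowed. The Participants section shows that recruitment has begun, and Study timeline says that it continues in waves, so later participants can still benefit.

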**Fig. 1 Fig1:**
[figure not shown]
Study Timeline

Participants will be recruited in waves over the study period depending on the capacity of available facilitators. An initial “soft launch” of the program was conducted with eight participants with sessions facilitated by [name] (registered clinical psychologist). Some minor changes to text (for clarity) were made to the BA intervention manual after the soft launch. Facilitators will have at least honours-level qualifications in psychology, or undergraduate psychology with previous experience working with diverse clients (e.g., through volunteer telephone counselling) as well as online training in administration of the MOCA-Blind. Facilitators will receive project-specific training in principles underlying BA, the application of BA in the context of promoting wellbeing (as opposed to treating depression), positive psychology interventions and the structure and administration of the sessions in both the treatment, and active control conditions. Training will take place in small groups over half-a-day, led by [name]. To reduce potential biases in administration across different facilitators, and to promote treatment fidelity, facilitators will complete a running sheet that includes a checklist of key content for each session across the BA and MCPPI conditions (running sheets are available upon request to the corresponding author).

### Good clinical practice

Informed consent will be obtained from all participants once the study procedures, risks and their rights have been explained to them. Additionally, participants will be informed of the limits to confidentiality. If they reveal information that suggests there is a risk of harm to themselves, or others, facilitators will be required to inform emergency services. In addition, facilitators will also be required to report suspected cases of child abuse or neglect to the child abuse report line. Ongoing supervision for facilitators will be provided by [name]. This study has been approved by the Flinders University Social and Behavioural Research Ethics Committee (Study no. 8172). This trial has also been retrospectively registered with the Australian New Zealand Clinical Trials Registry (ACTRN12621001192875), as was the pilot study (ACTRN12620000126910).

### Sample size and analysis

Sample size considerations were based on the numbers of participants needed to detect a medium effect size difference between the BA and active control groups on the LET at 1-week post intervention. This represents a difference of approximately 2-units on the LET based on previous research (possible scores range from 6 to 30) [32]. Positive psychology interventions have typically been found to have effect sizes in the small to medium range; for example, a recent meta-analysis reported values ranging from *g* = 0.39 to *g* = 0.62 across mental health and well-being outcomes [39]. Within this range, we deemed a medium effect as being a reasonable marker of meaningful change in life engagement, given that our exclusion criterion (see *Participants*) excluded those already scoring at or near the maximum on the LET. Using the Stata “power” module with alpha = 0.05 and a group difference of *d* = 0.52 indicated that 60 participants per group are required for power = 0.8. Data will be analysed using linear mixed models, which allow for dependencies among repeated observations, as is the case with pre- and post-test data (e.g., [63]). Models will be specified taking into account guidelines provided by Twisk et al. [64] for estimating treatment effects in randomised controlled trials. Specifically, a mixed model will be specified that includes dummy variables for time (contrasting baseline with 1-week and 3-month follow-ups) and interactions of time with treatment (BA vs. MCPPI) to estimate treatment effects at the first (1-week) and second (3-month) follow-ups. This approach controls for treatment group differences at baseline and makes use of all available data, with missing data accommodated under FIML assumptions [65].

## Discussion

Despite the importance of meaningful activity engagement in older adulthood, there are limited interventions available that are person-centred rather than activity specific. Interventions that can be tailored to the unique interests, values and capacities of individuals may represent a promising approach to enhancing older adults’ engagement with life. This study will test the efficacy of BA as a person-centred approach to promoting engagement with life in older adulthood. We see the promise of the BA approach as primarily arising from (a) the fact that it can be tailored to the unique circumstances of individuals, (b) its delivery not requiring a high degree of clinical expertise among facilitators ([66]), and (c) its principles of administration mapping onto processes of self-regulation that are recognised as supporting effective development across the life course [26, 28]. BA has been found to be effective in improving wellbeing in non-clinical samples [20, 23], but there is scarce research to date on whether BA-based approaches have utility in promoting engagement among community-dwelling older adults. BA will be compared to an MCPPI which will act as an active control condition, which makes use of evidence-based approaches to facilitating well-being [39, 67]. In addition to directly assessing the effectiveness of BA on promoting engagement with life, the study includes several novel secondary outcome measures (e.g., flourishing, goal disengagement and re-engagement, self-compassion) that will allow for exploration of whether the BA approach offers benefits to well-being above and beyond any benefits provided by the MCPPI.

## Data Availability

Once collected, deidentified data will be available from the corresponding author on reasonable request.

## Abbreviations

BA: Behavioural activation
BADS-SF: Behavioural Activation Depression Scale – Short Form
ELMS: Engagement, Life and Meaning Study
ELS-SF: Engaged Living Scale – Short Form
LET: Life Engagement Test
MCPPI: Multi-component positive psychology intervention
MOCA-Blind: Montreal Cognitive Assessment - Blind
UCLA Loneliness Scale: University of California Los Angeles Loneliness Scale
